## ***Statistical analysis***

All analyses will follow the Consolidated Standards of Reporting Trials (CONSORT) guidelines. Baseline measurements, group comparability, and descriptive characteristics will be assessed. Because patient dropout can occur for various reasons, data analyses will include both intention-to-treat (ITT) and per-protocol (PP) approaches. PP analysis considers only participants who complete the entire trial post-randomization, whereas ITT analysis includes follow-up data from all randomized participants. While PP analysis can exaggerate between-group differences, ITT analysis minimizes bias and loss to follow-up, generally producing more conservative estimates. Therefore, ITT analysis will be used as the primary method to prevent overstating effectiveness. The primary endpoint of interest is assessed after eight weeks of treatment.

All statistical analyses will be performed using IBM SPSS, version 26.0.1, with two-tailed tests ( $\alpha=0.05$ ) determining statistical significance. At baseline, categorical variables (e.g., sex, occupation, education level) will be compared between trial and control groups using chi-square tests. Continuous variables (e.g., age, BMI, pain intensity, duration of low back pain) will undergo a normality test. If the data follow a normal distribution, results will be expressed as mean  $\pm$  standard deviation (SD) and analyzed using independent-samples T-tests or Mann-Whitney U tests. Otherwise, the median (interquartile range) will be reported, and nonparametric tests will be applied. If the data meet the assumptions of homogeneity of variance and sphericity, a two-factor, three-level repeated-measures analysis of variance (group $\times$ time) will be conducted; otherwise, a mixed-effects model will be used.

According to the International Spine Conference, a two-point change in pain intensity (NRS scale: 0–10) signifies a minimum clinically important difference (MCID). Chi-square tests will compare the proportion of patients in each group who achieve MCID. Cohen's criteria will be used to evaluate the effect size across all outcome measures. No interim or subgroup analyses

are planned. An ITT approach will be used to address missing data for the primary outcome, and multiple imputation will minimize missing values.

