## **Abstract:**

**Purpose:** Telemedicine-based structured exercise programs have the potential to benefit patients with chronic low back pain (CLBP). However, evidence-practice gaps persist, including low exercise adherence and insufficient focus on mental health. Consequently, further research is warranted to clarify the impact of telemedicine-supported structured exercise programs on patients with CLBP.

**Patients and methods:** This randomized controlled trial will include patients with CLBP who have not received exercise therapy in the past three months. Participants in the trial group will receive patient education, health coaching, and home-based exercise therapy via mobile health (mHealth) applications loaded with wearable device integration. Those in the control group will receive conventional treatment, comprising patient education and written instructions for home exercises. Disability including pain intensity will be assessed as primary outcomes using the Roland-Morris Disability Questionnaire (RMDQ) and the Numerical Rating Scale (NRS) at baseline, 4 weeks, and 8 weeks. Statistical analyses will depend on assumptions such as homogeneity of variance and sphericity: if met, a two-factor, three-level repeated measures analysis of variance will be used; otherwise, a linear mixed-effects model will be employed.

**Keywords:** low back pain; telemedicine; exercise; study protocol; randomized controlled trial.

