## ***Sample size***

The sample size was calculated using G\*Power 3.1.9 under the following conditions: based on Cohen's standard for effect sizes, 0.2, 0.5, and 0.8 indicate small, medium, and large effects, respectively. A value of 0.3 was selected to represent a small-to-medium effect size, drawing on Murtezani's findings. With  $\alpha = 0.05$ , power = 0.8, and a correlation among repeated

measures of 0.5, a two-way repeated measures analysis of variance was planned, featuring three measurement points for each of the two groups. The resulting sample size was 58, and accounting for a 25% dropout rate increased the required sample size to 78 (total).

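### The primary model is chosen by assumption checks on the outcome data, and the test it names, an omnibus group-by-time interaction, does not test the week-8 difference that the protocol makes its primary endpoint

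*Protocol*

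**What the plan says.** The Abstract lets two assumption checks, on equal variances and on sphericity, decide the method: "if met, a two-factor, three-level repeated measures analysis of variance will be used; otherwise, a linear mixed-effects model will be employed". The Statistical analysis section repeats the rule: "If the data meet the assumptions of homogeneity of variance and sphericity, a two-factor, three-level repeated-measures analysis of variance" (group by time) is run, and if the assumptions fail a mixed-effects model replaces it. The three levels are baseline, week 4 and week 8, so baseline is one level of the outcome.

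On the endpoint, the same section says "The primary endpoint of interest is assessed after eight weeks of treatment", and the Outcome measures section also places the main evaluation of change after 8 weeks. ITT is primary, and on missing data the section says "An ITT approach will be used to address missing data for the primary outcome, and multiple imputation will minimize missing values".

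The Sample size section is built on the same ANOVA. It states "A value of 0.3 was selected to represent a small-to-medium effect size" and gives the assumed correlation and the test as "measures of 0.5, a two-way repeated measures analysis of variance was planned", with three measurements in each of two groups. The result is 58, raised to 78 for 25% dropout.

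**The concern.** Two things that the protocol fixes do not fit its stated aim.

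First, the group-by-time F test pools two contrasts among three visits. It can be significant because of week 4 alone, and a significant result gives no week-8 difference. The trial could report success on its primary test without having tested the endpoint it calls primary.

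Second, the primary model is known only after the outcome data have been checked. NRS and RMDQ could end up under different models, and the quantity reported for each is not settled in advance.

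A related cost is precision. Baseline NRS and RMDQ are measured in everyone, but baseline enters as a response level and not as a covariate.

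**Working it through.** **Inputs from the protocol.** Two-sided alpha 0.05, power 0.8, effect size 0.3 (metric not named), correlation 0.5, two groups at 1:1, three measurements, 58 evaluable, 25% dropout, 78 in total.

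**Assumed, because the protocol gives no SD and no week-8 difference.** Effects in SD units (0.6 as the main case, 0.5 and 0.8 as a range), equal SDs and compound symmetry unless stated.

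**1. The plan's own figure.** For the group-by-time interaction with k = 2 groups, m = 3 visits and f = 0.3, use λ = f²(N − k)(m − 1) with 2 and 2(N − 2) df. At N = 58, λ = 0.09 × 56 × 2 = 10.08 and power is 0.808; N = 57 falls just short of 0.80. So 58 is matched exactly. In this form the correlation is taken to be already inside f. The between-groups main effect would need 61, or 62 for equal arms. Dropout: 58/0.75 = 77.3, rounded up to 78. The trial is therefore sized on the omnibus interaction.

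**2. What the omnibus test responds to.** With group differences d at the three visits, λ = (N/4) × Σ(d − mean d)² / (1 − ρ), with 2 and 2(N − 2) df. At N = 58 and ρ = 0.5:

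- Week 4 only (0, 0.6, 0): Σ = 0.24, λ = 14.5 × 0.24/0.5 = 6.96, significant 64% of the time.
- Sustained (0, 0.6, 0.6): Σ = 0.24, λ = 6.96, 64%.
- Building up (0, 0.3, 0.6): Σ = 0.18, λ = 14.5 × 0.18/0.5 = 5.22, 51%.

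At N = 78 these become 78%, 78% and 65%. A vanished week-8 effect and a sustained one give the same rejection rate.

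**3. Baseline-adjusted week-8 comparison.** λ = (N/4) × d²/(1 − ρ²), with 1 and N − 3 df. At N = 58, λ = 14.5 × 0.36/0.75 = 6.96, power 74%. At N = 78, λ = 19.5 × 0.36/0.75 = 9.36, power 86%.

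**4. Range at N = 58, ρ = 0.5.** Each λ scales with d².

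| Week-8 effect (SD) | Omnibus, building up | Omnibus, sustained | Adjusted week 8 |
|---|---|---|---|
| 0.5 | 37% (λ 3.63) | 48% (λ 4.83) | 58% (λ 4.83) |
| 0.6 | 51% (λ 5.22) | 64% (λ 6.96) | 74% (λ 6.96) |
| 0.8 | 77% (λ 9.28) | 88% (λ 12.37) | 93% (λ 12.37) |

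For 80% power at 0.6 SD, the total analysed is 110 (building up) or 82 (sustained) for the omnibus test, and 68 for the adjusted comparison.

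**5. Where the gain disappears.** At ρ = 0.7, with 0.6 SD from week 4 on and N = 58, the omnibus λ = 14.5 × 0.24/0.3 = 11.6 gives 86%; the adjusted λ = 14.5 × 0.36/0.51 = 10.24 gives 88%. With SDs rising 1, 1.2, 1.4 and a raw difference of 0.6 from week 4, simulation (4,000 replicates) favours the omnibus test: 46% against 43% at N = 58, and 61% against 57% at N = 78.

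**6. The switch.** The same simulations assumed Mauchly's test, Levene's test at each visit and an unstructured fallback. The switch was triggered in about 15–18% of trials when both assumptions were true, and in about 93–98% when correlation decayed over time (0.5, 0.7, 0.3). Type I error of the two-step procedure was 4.6–5.5%.

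**The case against.** The best defence is that the plan is coherent on its own terms. The Sample size and Statistical analysis sections name the same test, 58 and 78 both reproduce, and both branches of the switch are declared beforehand. A group-by-time model contains a baseline-to-week-8 contrast, and a separate SAP could name it along with the covariance structure. That stands in part: missing modelling detail is no fault in a protocol. But a SAP cannot remove the switch without contradicting the protocol, and agreement between sizing and analysis only means that both address a hypothesis other than the week-8 endpoint.

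Three stronger readings are tempting, and the document does not support them.

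- A reader might infer that repeated-measures ANOVA discards everyone with a missing visit and so breaks ITT. The protocol plans ITT with multiple imputation, restricts only the per-protocol set to completers, and in Data management and auditing plans outcome collection after dropout. ANOVA on imputed data keeps all randomised participants. The open point is only how imputation and model are combined.
- A reader might infer that choosing the model from the data inflates type I error. The simulations did not show this.
- A reader might infer that the plan always wastes power. Step 5 shows cases where the loss is negligible or reversed.

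**Conclusion.** The concern holds in limited form. The primary test does not test or estimate the week-8 difference, and the primary model is not fixed before the outcomes are seen. The first point does not depend on power: under compound symmetry the omnibus test rejects equally often whether a week-4 effect lasts or is gone by week 8 (64% at N = 58 for 0.6 SD, correlation 0.5). The harm of the switch is uncertainty about which model and which quantity will be reported.

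The power gain is secondary and conditional. At 0.6 SD and correlation 0.5 it is 51–64% against 74% with 58 analysed, and 65–78% against 86% with 78. It rests on assumed effects, is small at correlation 0.7 with an early effect, and can reverse if variance rises over time.

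**What to change.** In the Abstract and Statistical analysis section, delete the assumption-test switch. Pre-specify one model for both NRS and RMDQ in all randomised participants: a mixed model for repeated measures on weeks 4 and 8 with group, time, group by time and the baseline value as covariate, or ANCOVA at week 8. Name the week-8 group difference with 95% CI as the primary result. State how multiple imputation is used with that model, for example as a sensitivity analysis.

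In the Sample size section, restate the power that the planned 78 gives for this contrast, using a justified SD and difference, without enrolling more.

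No new data are needed, but the change is not free. The sample-size justification must be rewritten, and the restated power may be below 80%: at 0.6 SD and correlation 0.5, 68 analysed are needed, while 25% dropout from 78 leaves 58 (74%). Power could also be slightly lower than with the omnibus test if the effect is early and variance rises.

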## **Setting & Recruitment**

Participants will be recruited from the Specialist Outpatient Clinic at West China Hospital, Sichuan University. Individuals who meet the eligibility criteria will be informed about the trial procedures and enrolled upon providing written informed consent; those who do not meet the criteria will receive standard treatment in accordance with the trial protocol. To ensure an

adequate sample size, standardized training and supervision will be provided to researchers, improving the success rate of informed consent acquisition. The trial aims to recruit 78 participants, and additional strategies (e.g., referrals from medical examination centers or relevant departments, poster campaigns) will be employed to facilitate timely enrollment. Recruitment will commence within one year of the scheduled enrollment date and will proceed based on site readiness. Details on data collection and intervention administration are available in Supplemental Material II. All eligible participants who agree to partake in the trial will be randomly assigned and briefed on the required procedures and written informed consent (accessible in Supplemental Material III) must be provided prior to enrollment. Baseline data for both groups will be gathered via a questionnaire administered before the intervention in Room 902 of the Special Needs Outpatient Department, collecting demographic information (e.g., gender, age, height, weight, occupation, education), potential causes of back pain, physical activity level, medical and exercise treatment history, duration of low back pain, severity of low back pain (current, worst, and least), level of functional impairment, and types of pain avoidance behaviors (see Supplemental Material II). Experienced physical therapists, who are independent of the trial design, intervention, and statistical analysis, will perform outcome measurements at baseline, after the 4-week intervention, and after the 8-week intervention, as illustrated in Figure 1.

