## Primary outcomes

CLBP severity will be measured using the Numerical Rating Scale (NRS), which ranges from 0 (no pain) to 10 (severe pain). Patients select a single number (0–10) that best represents their current level of pain. The NRS is widely used due to its simplicity, ease of administration, and reliable detection of pain severity.

The Roland Morris Disability Questionnaire (RMDQ) evaluates functional status in patients with low back pain. It consists of 24 items specifically related to limitations caused by low back pain. Each item is scored as 1 (yes) or 0 (no), yielding a total score between 0 and 24, where higher scores indicate greater functional impairment.

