| Pain lasts 12 weeks or more.                                                                                                         | Cognitive impairment results in the inability to understand the physical therapist's instructions and the content of the app.                            |
| Pain intensity (when the worst pain) $\geq 3$ on the Numeric Rating Scale (NRS).                                                     | Pregnant or breastfeeding.                                                                                                                               |
| Ability to operate a smartphone.                                                                                                     | History of spine surgery.                                                                                                                                |
| Voluntarily participate in the trial and sign the informed consent.                                                                  | Patients who have received exercise therapy in the past three months for low back pain.                                                                  |
| Accepted randomization.                                                                                                              | Patients with severe cardiovascular and cerebrovascular diseases.                                                                                        |
| Candidates who meet all the above criteria will be included                                                                          | Candidates meeting any of the above criteria will be excluded                                                                                            |

616

617

618 **Table 2 Core stability training & Motor control training**

| Exercise (R=Repetition, S=Second)                                   | Sets and Repetitions per Week |     |           |     |
|---------------------------------------------------------------------|-------------------------------|-----|-----------|-----|
|                                                                     | 1-4 Weeks                     |     | 5-8 Weeks |     |
|                                                                     | Set                           | R/S | Set       | R/S |
| Core stability training                                      |                               |     |           |     |

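### The NRS responder comparison is an unadjusted chi-square test: valid, but less precise than one that uses the baseline NRS already recorded for every participant

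*Protocol*

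**What the plan says.** The protocol's Statistical analysis section treats "a two-point change in pain intensity" on the 0-10 NRS as the minimum clinically important difference and then fixes the test: "Chi-square tests will compare the proportion of patients in each group who achieve MCID". No adjusted responder analysis is named. The sentences on this comparison state neither the direction of the change nor the visit, although the same section places the primary endpoint at eight weeks.

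Under Primary outcomes, the NRS score is current pain: "Patients select a single number (0–10) that best represents their current level of pain". The Abstract and Table 3 have it measured before treatment as well as after: "Numerical Rating Scale (NRS) at baseline, 4 weeks, and 8 weeks". Table 1 sets the entry threshold on worst pain (at least 3), not on current pain. Randomization and blinding describes permuted blocks of four and states no stratification by baseline pain. The repeated-measures model includes baseline NRS as a time level, but only for the continuous score.

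**The concern.** Response here is a change from baseline on a bounded integer scale. A patient whose current pain is 0 or 1 cannot fall by two points, and the entry rule does not exclude such a patient. Above that floor, regression to the mean makes a two-point fall easier from a high score than from a low one. So baseline NRS predicts response, and a comparison of raw proportions leaves that variation in the error.

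The trial is small (78 randomised), and this is the only analysis in the protocol that ties a primary outcome to a clinical threshold. At stake are some of its power and how far its estimate moves with the baseline scores that chance deals to each arm.

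**Working it through.** **The plan's own figure.** The Sample size section gives 58, raised to 78. With f = 0.3, α = 0.05, two groups (k = 2) and three times (m = 3), the group × time test under the SPSS-style effect-size option has λ = f²(N − k)(m − 1) = 0.09 × 56 × 2 = 10.08 at N = 58, and power 0.808. Then 58/0.75 = 77.3, rounded up to 78. Both figures reproduce. They belong to the continuous analysis; the protocol states no power or response rate for the responder test.

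**Inputs.** From the protocol: the responder threshold, the 0-10 integer scale, 1:1 allocation, two-sided α = 0.05, and 39 per arm (29 after the planned 25% dropout). Assumed: baseline mean and SD, baseline to week-8 correlation r, mean fall in controls, and extra fall in the trial group. The protocol has only a general repeated-measures correlation of 0.5 and a standardised effect of 0.3, neither tied to the NRS.

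**Model.** Week-8 score = mean − fall − effect × arm + r × (baseline − mean) + error, with error SD = SD × √(1 − r²). Scores are rounded and clipped to 0-10. Response means baseline minus week 8 is at least 2.

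**Step 1: dependence on baseline.** With mean 5, SD 2, r = 0.5 and a control fall of 1.5, the control response rate is 0 at baseline 0-1, 0.28 at 3, 0.50 at 5, 0.72 at 7 and 0.88 at 9. For means of 4-5, SDs of 1.5-2 and r of 0.3-0.7, the correlation between baseline NRS and response is 0.28 to 0.52.

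**Step 2: power.** Chi-square against a baseline-adjusted risk difference with robust standard error, 3,000 simulated trials per row:

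| Mean, SD, r, control fall, effect | 39 per arm | Gain (points) | 29 per arm | Gain (points) |
|---|---|---|---|---|
| 5, 2, 0.5, 0.5, 1 | 40.8% → 46.2% | 5.4 | 31.1% → 35.7% | 4.6 |
| 5, 1.5, 0.5, 0.5, 1 | 61.0% → 69.4% | 8.4 | 47.2% → 54.7% | 7.5 |
| 5, 2, 0.5, 1, 1.5 | 71.8% → 78.3% | 6.5 | 57.6% → 66.6% | 9.0 |
| 6, 1.5, 0.5, 1, 1 | 64.0% → 70.4% | 6.4 | 50.7% → 58.7% | 8.0 |
| 5, 2, 0.85, 1.5, 1 | 81.0% → 83.3% | 2.3 | 64.5% → 69.9% | 5.4 |
| 5, 2, 0.5, 1.5, 0.5 | 14.4% → 15.2% | 0.8 | 11.0% → 13.1% | 2.1 |
| 5, 1.5, 0.9, 1.5, 0.7 | 88.2% → 89.0% | 0.8 | 75.3% → 78.5% | 3.2 |

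The estimator proposed below fits logit P(response) = a + b × arm + c × baseline. It then averages, over all patients, the predicted probability under trial minus that under control. With mean 4.5, SD 2.2, r = 0.5, control fall 1.0 and effect 1.3, it raised power from about 49% to 57% at 39 per arm. Across the settings run at that size its gain was about 2 to 9 points.

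**Step 3: is the comparison fair?** Type I error was 4-6% for chi-square, 4.7-6.0% for the standardised risk difference and 5-7% for the likelihood-ratio logistic test. With the tests calibrated to equal size, the gain was about 4 to 10 points at 39 per arm and 3 to 9 at 29 per arm.

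**Step 4: chance imbalance.** The standard error of the baseline difference is SD × √(2/39). For SD 2 this is 2 × 0.226 = 0.45 NRS points. With mean 5 and r = 0.5, the response probability rises 0.106 per baseline point, so a one-standard-error imbalance shifts the observed difference by 0.45 × 0.106 = 4.8 percentage points with no treatment effect. Across settings the slope was 9-12 percentage points per NRS point in one set of runs; with imbalances of 0.41-0.49 that gives 0.41 × 9 = 3.7 to 0.49 × 12 = 5.9. After adjustment the slope was about zero.

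**The case against.** The strongest reply is that nothing is invalid. A chi-square test of two randomised proportions holds its size, and choosing an unadjusted supporting analysis is an efficiency preference. That stands, and it limits the weight. It does not remove the point, because the protocol names the test outright instead of leaving it open.

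Four stronger readings are tempting and not supported:

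- **Bias or false positives.** A reader might infer that chance imbalance makes the responder result false. The chi-square standard error already includes that variation, which is why its type I error stays near 5%. The planned baseline comparison, which includes pain intensity, may reveal an imbalance but does not adjust for it.
- **A fixed loss of up to about 15 points.** Gains of that size come from the likelihood-ratio test, which is slightly liberal, and every NRS input is assumed. For an adjusted risk difference with robust standard error, one wider grid ran from about 1 to 14 points.
- **Baseline NRS as the dominant predictor.** The protocol gives no data on this and no other predictor was compared. Only a material dependence is shown.
- **Multiple imputation requires a logistic model.** A chi-square p-value does not pool directly, but an unadjusted risk difference and its standard error pool by Rubin's rules as well.

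It is also fair that dichotomising costs more than omitting the covariate. In the setting with mean 4.5, a simple change-score comparison had 67% power, against 50% for chi-square and 58% for logistic regression. The continuous analysis remains in the plan, so the main inference does not depend on this test.

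**Conclusion.** The point holds as one of efficiency. The responder test ignores a recorded baseline value on which response materially depends. Adjustment is worth roughly 2 to 10 percentage points of power under plausible inputs, falling to about 1 where power is near its floor or ceiling or the correlation is about 0.9. It also removes the conditional shift of about 4 to 6 percentage points per standard error of baseline imbalance. These sizes rest on assumed NRS means, SDs, correlations and effects; the direction follows from the bounded scale and the change-from-baseline definition. Because the comparison is supportive and did not set the sample size, the weight is minor to moderate.

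**What to change.** Replace the chi-square sentence in the Statistical analysis section with:

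> MCID response (a fall of at least 2 NRS points from baseline to week 8) will be compared between groups by logistic regression on group and baseline NRS, reported as a covariate-standardised risk difference with a robust 95% CI, pooled over the imputations.

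Keep the raw proportions and the chi-square test as description or a sensitivity analysis. The new sentence also settles the direction and the visit. It needs no new data, visits or patients. The cost is slightly more analysis work, because the standardised risk difference needs a short calculation beyond the logistic model.
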